## Analyses

3

Analyses of change in the primary and secondary outcomes will be conducted on an intention-to-treat (ITT) basis using all randomised participants. The changes in the primary and secondary outcomes will be tested using general linear mixed effects regression models with repeated measures (MMRM; MIXED Procedure in SPSS 22 and STATA 15). These models will include the random intercept for each individual participant and fixed effects for condition (intervention [sleep] vs placebo [nutrition]) and assessment period (baseline, intervention, and 6-month follow-up). Where appropriate, adjustments for demographic variables will be made via their inclusion as additional fixed effects. The outputs of analyses will be reported via significance (as confidence intervals) and magnitude estimates to guide clinical interpretation.

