#### Trial objectives

1.1.1

The primary trial objective is to test the effectiveness of a sleep extension and education intervention on objective indices of sleep and risky driving performance of chronically sleep-deprived young adults (18–24 years old).

The secondary objective of the trial is to assess the effects of the sleep extension and education intervention on daily subjective indices of sleep, and other risk factors for adverse driving outcomes (e.g., higher order cognitive functions, alcohol use, stress, and mood).

We hypothesise that, in comparison to the placebo control group, the intervention group will;(1)increase their habitual sleep duration by at least a clinically meaningful 25 min per night on average,(2)decrease their frequency of acute sleep loss episodes (<6 h s of sleep) across a typical week,(3)demonstrate reductions in high risk driving performance on the road and in the driving simulator.(4)improved performance on computerised executive-function tasks associated with behavioural self-regulation.

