#### Sample size

1.1.2

A minimum sample size of 189 participants was initially calculated. We will aim to recruit 210 participants, allowing for ∼10% attrition at follow-up (consistent with drop-out from our previous studies in this age cohort). Based on the authors’ previous studies using the same measurement approach (h^2^_p_ = 0.12–0.37) [38], this sample size will provide 90% power, with a significance level of *p* = 0.05, to detect a 'small’ change in the primary driving outcome based on a parallel groups design with 0.3 correlation among the repeated measures. In addition, this sample size will provide 90% power to detect a 'small-medium effect size’ of a 5% increase in mean objective sleep duration (primary sleep outcome - equivalent to approximately 25 min additional sleep per night). This is a clinically and physiologically significant change [39], representing almost three extra hours of sleep each week. Based on our previous laboratory work [38] the study is also sufficiently powered for all proposed secondary outcomes.

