## Trial intervention group: sleep extension and education

2

The aim of the intervention is to increase habitual sleep duration. Following the baseline assessment period, participants randomised into the sleep condition will be provided an individualised sleep extension and education session with an experienced sleep researcher. The sleep extension and education sessions consist of three core elements:(1)Sleep scheduling: This component is based on behavioural principles for sleep scheduling [40]. The researcher will use sleep data collected from actigraphy during the participants' baseline assessment to calculate the participants' average bedtime, wake-up time and habitual nightly sleep duration. Based on these calculated estimates, participant will be 'prescribed’ an extra 20% of time to be spent in bed at home each night across the 3-week intervention period. To facilitate uptake of the intervention into existing sleep/lifestyle routines, participants will be asked to go to bed 15 min earlier each night gradually until their bedtime matches the additional 20% prescribed (this transition may take anywhere between 3 and 7 days). Participants will be asked to maintain this new 'time-in-bed’ for two more weeks. The total intervention period therefore spans 3 weeks (1 week of transitioning to the new sleep schedule, and 2 weeks of maintaining the new schedule). For example, a participant with an average bedtime of 11:30pm, and an average habitual nightly sleep duration of 6.5 h will be prescribed an additional 1.3 h ‘in-bed’ time each night, to be achieved gradually by going to bed 15 min earlier each night until it matches 10:10pm.(2)Sleep Education Online modules: Participants will view 4 × 10-min educational video vignettes (purpose-developed by research team) providing basic education about sleep and sleep health. The topics covered include a) The fundamentals of sleep & circadian functions; b) The benefits of sleep for physical performance, road safety, cognitive and physical functioning; c) The benefits of good sleep for mental health & social functioning and d) The 'SIMPLE’ strategies; Practical tips and tools for supporting healthy sleep. These tips and tools were purpose-developed by the research team and centred on healthy sleep hygiene principles. The SIMPLE strategies include information about sleep 'Scheduling’ and regularity, 'Implementing a pre-bed routine’, 'Minimising screen time’ in the hours before bed, making lifestyle changes aimed at 'Prioritising sleep’, 'Learning to manage stress', and understanding how to make your 'Environment’ conducive to sleep. Participants view the video vignettes at their initial sleep scheduling session and are provided links to the videos via reminder text messages at two other time points in the intervention period (end of Week 1, and 3) encouraging them to revisit this content in their own time.(3)Motivational interviewing and sleep pledge: After viewing the online modules, and receiving their new sleep schedule, the researcher will use motivational interviewing techniques to explore participant's self-efficacy, self-reported sleep needs and/or self-reported barriers to managing sleep health and timing. Using the framework of the 'SIMPLE’ strategies for improving sleep, participants will be provided with their new sleep Schedule, and asked to reflect on which two of the remaining 5 'SIMPLE’ strategies they would be able to commit to and implement for the duration of the intervention period. This process will facilitate autonomy and self-efficacy around sleep scheduling and timing, encouraging maximum fidelity to the intervention sleep schedule. To facilitate participant retention and commitment to the intervention schedule, participants will be asked to sign a 'pledge’ of their commitment to their agreed upon sleep schedule and choice of sleep improvement strategies for the duration of the intervention.

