### Primary outcome 1: risky driving performance

2.2

On-road risky driving performance will be assessed using small, sensitive, 3-axis accelerometers (GeneActiv Original, ActivInsights). The accelerometer is placed in a zip lock bag on a flat surface in the boot/trunk of the participant's vehicle and secured with duct tape. The device is oriented so that: x captures forwards-backwards acceleration, y captures left-right acceleration, and z captures up-down acceleration. These devices objectively record vehicular forces of acceleration from discrete vehicle events in forward and lateral directions, e.g., overcorrection after attentional drifts when drowsy [43] and provide an ecologically meaningful assessment of driving performance [44]. Previous research suggests that elevated g-force events have high predictive accuracy for crash and near-future crashes in young adults [43], and therefore provide a proxy measure of risky driving in young drivers [45].

Risky driving indices (elevated g-force events) extracted from these devices for analysis will include;−Rapid starts (throttle acceleration): defined as forward acceleration (m/s^2^),−Hard stops: defined as longitudinal acceleration due to braking (m/s^2^),−Hard left turns: defined as lateral acceleration to the left side (m/s^2^), and−Hard right turns: defined as lateral acceleration to the right side (m/s^2^).

Extending on prior research [43], a custom composite ‘risky driving variable’ will be created from these g-force indices and taking into consideration each participant's driving data per day and aggregated across the week, and at times of increased driving risk (e.g., driving at night/in the morning and at the circadian nadir). Changes in the risky driving composite from baseline to post-intervention will be used in primary analyses.

To minimise the risk of use by other drivers, participants will 1) be included in the study if they own their own private vehicle, 2) be asked to refrain from lending their vehicle to others during the study periods, and 3) complete a driving diary. Further, validation between wrist and car actigraphy is planned in secondary analyses of the study.

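### The listed fixed effects contain no condition-by-period term or baseline adjustment, so the model as written does not estimate the between-arm difference in change that the trial is meant to test

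*Protocol article*

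**What the plan says.** Section 3 (Analyses) of the protocol article states the aim of the modelling: "The changes in the primary and secondary outcomes will be tested using general linear mixed effects regression models with repeated measures". It then lists the terms. On the random side: "These models will include the random intercept for each individual participant". On the fixed side: "fixed effects for condition (intervention [sleep] vs placebo [nutrition]) and assessment period (baseline, intervention, and 6-month follow-up". The only further terms are demographic: "adjustments for demographic variables will be made via their inclusion as additional fixed effects", and these apply where appropriate.

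Three other places define what the model has to deliver:

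- Section 2.2 (Primary outcome 1: risky driving performance): "Changes in the risky driving composite from baseline to post-intervention will be used in primary analyses".
- Section 1.1.1 (Trial objectives), where the hypotheses compare the intervention group with the placebo group. The first is that it will "increase their habitual sleep duration by at least a clinically meaningful 25 min per night on average".
- Section 2 (Trial intervention group), which puts treatment after the first measurement period: "Following the baseline assessment period, participants randomised into the sleep condition will be provided an individualised sleep extension and education session".

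Nowhere does the article mention a condition-by-period interaction, the baseline value as a covariate, or equal baseline means by constraint.

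**The concern.** A model with condition and period as main effects only assumes that the arms differ by the same amount in every period, including the one before treatment. It has one parameter for the arm difference and none for how that difference changes over time. Yet the objectives and the primary driving analysis are about exactly that: whether one arm changes more than the other between baseline and post-intervention.

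An analyst who fits the listed terms would report a condition coefficient that mixes a pre-treatment period with two post-treatment periods. Three consequences follow:

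- The reported effect is smaller than the true post-intervention effect. Section 3 promises magnitude estimates for clinical interpretation, and 25 min is the article's own threshold for a meaningful gain, so an intervention that exactly reached it would appear to fall short.
- The post-intervention effect and the 6-month effect are merged into one number.
- A baseline difference that arises by chance enters the treatment estimate.

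**Working it through.** **Inputs from the article.** Three assessment periods with baseline as a level, a random intercept, and main effects of condition and period (Section 3). Target sleep effect 25 min per night, read as a between-arm difference (Section 1.1.1). Section 1.1.2 (Sample size) gives a minimum N of 189, recruitment of 210 for about 10% attrition, 90% power, significance level 0.05, and a "parallel groups design with 0.3 correlation among the repeated measures".

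**Assumptions.** Two-sided test, two equal arms, equal numbers in each period, and equal variance and correlation across periods (as a random intercept implies). Effects in SD units are assumed, because the article gives no SD.

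**The plan's own figure.** 189/(1 − 0.10) = 210, which reproduces. The 189 itself cannot be checked: the small effect has no number and no SD is given. Nothing below depends on how it was obtained.

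**Step 1. What the condition coefficient estimates.** With balanced data it equals the mean of the three period-specific arm differences. Randomisation makes the expected baseline difference zero, so

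E(condition) = (0 + d_post + d_fu)/3.

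| True effect, post / 6 months | Condition coefficient | Change contrast at post |
|---|---|---|
| 25 / 25 min | 50/3 = 16.7 min | 25 min |
| 25 / 12.5 min | 37.5/3 = 12.5 min | 25 min |
| 25 / 0 min | 25/3 = 8.3 min | 25 min |

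The fractions 2/3, 1/2 and 1/3 need no SD and no value for the correlation.

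**Step 2. Standard errors in SD units, correlation 0.3, N = 189.**

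- Mean of three periods: variance (1 + 2 × 0.3)/3 = 0.533, so SE = √(0.533 × 4/189) = 0.106.
- Change from baseline: variance 2(1 − 0.3) = 1.4, so SE = √(1.4 × 4/189) = 0.172.
- Post value adjusted for baseline: variance 1 − 0.3² = 0.91, so SE = √(0.91 × 4/189) = 0.139.

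**Step 3. Power for an assumed post-intervention effect of 0.558 SD (about 0.56).** This size is chosen because it gives the interaction contrast 90% power: 0.558/0.172 = 3.24.

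| Effect at 6 months | Condition coefficient | Divided by 0.106 | Power |
|---|---|---|---|
| None | 0.186 | 1.75 | about 42% |
| Half | 0.279 | 2.63 | about 75% |
| Full | 0.372 | 3.50 | about 94% |

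**Step 4. Check by simulation.** 4,000 trials, 94 per arm, correlation 0.3, variances treated as known, and 25 min set at 0.5 SD (an assumed SD of 50 min).

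| Scenario | Listed model: estimate, rejection | Interaction contrast at post | Baseline-constrained at post |
|---|---|---|---|
| Effect sustained | 0.331 SD, 87% | 0.496 SD, 81% | 0.496 SD, 94% |
| Effect at post only | 0.166 SD, 34% | 0.500 SD, 82% | 0.499 SD, 95% |
| No effect | 0.001 SD, 4.7% | −0.001 SD, 5.4% | 0.000 SD, 4.9% |

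The estimates match the fractions in Step 1, and the rejection rate with no effect stays near 5%.

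**Step 5. Baseline imbalance.** With no treatment effect and an imposed 0.15 SD difference in all three periods, the listed model estimates 0.151 SD and rejects in 29% of trials. The interaction contrast estimates 0.004 SD and rejects in 5%. The baseline-constrained model removes only part of so persistent a difference (0.108 SD, 12%). This scenario is conditional on an imbalance fixed in advance. A chance baseline difference b is instead expected to shrink to 0.3b later, so the listed model carries (b + 0.3b + 0.3b)/3 = 0.53b into its estimate.

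**The case against.** The strongest reply is that the list need not be complete. The article says what the models will include, not that they contain nothing else. The sentence before it speaks of testing changes, and Section 2.2 speaks of change from baseline. A purely additive model cannot test differential change, so the charitable reading is that the interaction is intended and unlisted. This is also a condensed article, and the full protocol and analysis plan are not shown. That reading is plausible, and it rules out saying that the interaction has been left out of the trial's actual analysis. It does not remove the defect in the text. The article chose to enumerate the fixed effects down to the factor levels, and the enumerated set does not match the analysis announced in the same paragraph.

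Two stronger conclusions are tempting and not supported:

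- *That power collapses.* The 42% against 90% comparison is the case where the effect has vanished by 6 months. With a fully sustained effect the condition term has about 94% power, above the interaction contrast's 90%, and the simulation shows the same reversal (87% against 81%). Power depends on persistence, which the article does not predict.
- *That the model produces false positives.* Over randomisations the test keeps its type I error. The 29% in Step 5 describes one fixed, persistent imbalance, and an unadjusted post-only comparison has a similar exposure.

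It is also fair to say that the 25 min figure belongs to sleep, which Section 2.3 labels the initial secondary outcome although other sections call it primary. The driving composite has no numerical target, so its dilution can be given only as a fraction.

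**Conclusion.** The point stands as a mis-stated model. As listed, the terms include no parameter for the between-arm difference in change, and the condition coefficient recovers one third to two thirds of a post-intervention effect as persistence runs from none to full: 8.3 to 16.7 min of a true 25 min. The fractions rest on balanced data and on randomisation making the expected baseline difference zero. Roughly 10% attrition would alter them somewhat but not their direction. The harm is a diluted estimate and a merged time point, with a chance baseline difference partly carried into the result. The power figures of about 42%, 75% and 94% rest on the assumed 0.56 SD effect, a two-sided 5% test, N = 189 and correlation 0.3. A reader should not infer inflated type I error, a general loss of power, or certainty that the investigators intend the additive model.

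**What to change.** In Section 3, add condition by assessment period to the fixed effects. If it was always intended, say so. Preferably go one step further and use baseline properly, in either of two ways:

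- keep baseline as an outcome level but constrain the arm means to be equal there, or
- use the baseline value as a covariate, with only the post-intervention and 6-month periods as outcomes.

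At a correlation of 0.3 these are more precise than the plain change contrast: the SE is 0.139 against 0.172 SD in Step 2, and simulated power is 94–95% against 81–82% in Step 4.

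For the driving composite, name the arm difference in change from baseline to post-intervention as the primary contrast, in line with Section 2.2, and the 6-month contrast as secondary. Apply the same model to the sleep outcomes. Whether sleep is primary or secondary is a separate matter that this change does not settle.

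The cost is a sentence or two of analysis wording, best written before the statistician sees outcome data by arm. No new data, visits or participants are needed.

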## Discussion

4

Driving while sleepy represents a critical risk for young drivers. This protocol describes the design of a pragmatic randomised control trial aimed to increase sleep and decrease sleepiness-related road crashes in young adults aged 18–24 years. This study will generate new knowledge about the effectiveness of a sleep extension intervention for reducing risky driving performance in young adults, a cohort at increased risk of sleepiness related road crashes. Secondary analyses, including examination of more complex sleep and circadian components are a critical and planned component of the study and will be explored on a case-by-case basis. This intervention is designed with pragmatic and cost-effective implementation as a major consideration. As such, if effective, this intervention has the potential to be widely and efficiently implemented on a public health level through a range of pathways (e.g., government mandated education about the benefits of sleep for road safety). In turn, widespread policy shift towards prioritising sleep may lead to a reduction in road trauma in young drivers, with subsequent reductions in the medical, industrial, and social costs associated with sleepiness related road-crashes.

### Strengths and limitations

4.1

There are both strengths and limitations of the proposed study. One strength is the use of standardised and objective measures of sleep and driving in a population of community-dwelling young adults allowing naturalistic, real-time measures of both primary outcomes. Additionally, this is an intensive study which employs a range of measurement techniques to evaluate a range of primary and secondary outcomes including, sleep, risky driving, cognition and risk-taking behaviours. Generalisability of the findings and content of the intervention are specific to self-identifying sleep deprived young adults. However, flexibility of the design should allow it to be successfully adapted for implementation in other settings and groups.

## Conclusion

5

Young adults are overrepresented in fatigue related road vehicle crashes. However, research and road safety strategies have fallen short in providing answers on how to best tackle this problem. Results from this pragmatic randomised control trial will potentially provide a framework for the successful implementation of a cost-effective and efficient sleep extension protocol to reduce fatigue-related crashes in young adults.

## Ethics declaration

This study was reviewed and approved by the University of Queensland Human Research Ethics Committee, with the approval number: 2019/HE001269. All participants provided informed consent to participate in the study. Furthermore, all participants provided informed consent for the publication of their anonymized case details and images.

## Data availability statement

There is no data presented in this publication. As such, please contact the research team regarding data availability.
